**Appendix 1 List of participating study sites for JFMC33-0502**

**APPENDIX 2 Patient briefing materials/Informed Consent Form**

**ATTACHMENTS Case report forms**

# **0. Study Overview**

## **0-1. Schema**

Stage III (Dukes’ C)

Colorectal Cancer, Sigmoid Colon Cancer Cases

Curative Resection “Cur A”

Group Randomization

**Group A: Standard-of-Care**

Capecitabine 2 weeks on, 1 week off

8 courses (approx. 6 months)

**Group B: Study Treatment**

Capecitabine 2 weeks on, 1 week off

16 courses (approx. 12 months)

## **0-2. Study Objectives**

The purpose of this study is to determine the optimal dosing period of capecitabine as postoperative adjuvant chemotherapy in cases of Stage III (Dukes’ C) colorectal cancer and sigmoid colon cancer involving curative resection by comparing patients receiving 8 courses (approximately 6 months) of the standard-of-care therapy consisting of capecitabine administered in a 2 weeks on, 1 week off schedule (Group A) with patients receiving 16 courses of capecitabine (approximately 12 months) on the same dosing schedule (Group B).

Primary Endpoint:

Disease-free survival (DFS) period

Secondary Endpoints:

(1) Relapse-free survival (RFS) period

(2) Overall survival (OS) period

(3) 2-year DFS rate

(4) Adverse event frequency and severity

(5) Treatment compliance

(6) HRQOL (Health-related Quality of Life)/Medical Economy　*Tertiary study conducted by capable study sites

## **0-3. Cases Targeted**

**0-3-1. Inclusion Criteria**

1) Patients with histologically diagnosed colon cancer (adenocarcinoma)

2) Cases of histological Stage III* colorectal cancer or sigmoid rectal cancer

*as defined in the Treatment Guidelines for Colorectal Cancer (7th edition)

3) Colorectal cancer cases in which resective surgery was performed (including cases involving D2 or higher lymph node dissection)

4) Cases in which surgery was determined to have achieved cure degree A (Cur A)

5) Patients aged (at time of enrollment) between 20 and 80 years

6) Performance status (PS) (Eastern Cooperative Oncology Group [ECOG]): 0 or 1

7) Eligible patients who have not yet undergone chemotherapy or radiotherapy

8) Patients capable of taking meals

9) Patients maintaining stable vital organ functions

a) WBC count ≥ 3,000/mm3 and <12,000/mm3

b) Hemoglobin ≥ 9.0 g/dL

c) Thrombocyte count ≥ 90,000/mm3

d) Serum creatinine ≤ 1.5x hospital standard upper limit

e) Total serum bilirubin ≤ 1.5x hospital standard upper limit

f) AST, ALT ≤ 2.5x hospital standard upper limit

g) ALP ≤ 2.5x hospital standard upper limit

10) Creatinine clearance* >50 mL/min

*: Determined based on the following simple formula to calculate creatinine clearance

Men: [(140-age)×body weight (kg)]/[72×serum creatinine value (mg/dL)]

Women: [(140-age)×body weight (kg)×0.85]/[72×serum creatinine value (mg/dL)]

11) Cases in which the protocol treatment was initiated within 8 weeks after surgery

12) Patients who consented to study participation in writing

**0-3-2. Exclusion Criteria**

1) Patients who are pregnant or nursing, or who may become pregnant

2) Patients who have a history of hypersensitivity or who have developed severe adverse events as a result of fluoropyrimidine drug use

3) Patients who have undergone organ transplantation

4) Patients who have serious complicating conditions (interstitial pneumonia, pulmonary fibrosis, intestinal palsy, intestinal obstruction, poorly managed diabetes, cirrhosis, poorly managed hypertension, history of myocardial infarction within the prior 6 months, unstable angina, etc.)

5) Patients with multiple active* (*defined as cases with a disease-free period shorter than 5 years) cancers (excluding resolved skin basal cell carcinoma and cervical cancer, or gastric, esophageal, and M colon cancers confirmed to have been resolved as a result of endoscopic mucosal resection)

*“Multiple cancer” is a blanket term encompassing both “multifocal” and “duplicative” cancers [Treatment Guidelines for Colorectal Cancer (7th edition)]

6) Patients with uncontrollable advanced complicating infection

7) Patients otherwise deemed unsuitable for participation in this clinical trial by a physician

## **0-4. Treatment Procedure**

**0-4-1. Group A: Standard-of-care group (8 courses [approx. 6 months])**

Capecitabine (Xeloda tablets): Patients will receive the established dosage of capecitabine (1,250 mg/m2) based on their total body surface area (1,500 mg–2,400 mg) twice daily (after breakfast and within 30 minutes after dinner) for 14 days continuously followed by a 7-day off period. This 3-week period will comprise 1 course of treatment. Patients will receive 8 courses in total.

After completing all 8 courses, patients not exhibiting cancerous recurrence will undergo continuous monitoring without additional treatment.

**0-4-2. Group B: Study treatment group (16 courses [approx. 12 months])**

Capecitabine (Xeloda tablets): Patients will receive the established dosage of capecitabine (1,250 mg/m2) based on their total body surface area (1,500 mg–2,400 mg) twice daily (after breakfast and within 30 minutes after dinner) for 14 days continuously followed by a 7-day off period. This 3-week period will comprise 1 course of treatment. Patients will receive 16 courses in total.

After completing all 16 courses, patients not exhibiting cancerous recurrence will undergo continuous monitoring without additional treatment.

**0-4-3. Established Capecitabine Dosages**

Per-administration capecitabine dosages

by subject body surface area (Groups A and B)

| Body Surface Area | Single-dose Volume |
| --- | --- |
| ≤1.33 m2 | 1,500 mg (5 tablets) |
| ≥1.33 m2 ≤1.57 m2 | 1,800 mg (6 tablets) |
| ≥1.57m2 ≤1.81m2 | 2,100mg (7 tablets) |
| ≥1.81m2 | 2,400mg (8 tablets) |

## **0-5. Study Period and Target Number of Subjects**

Target number of subjects: 600 subjects per group, 1200 in total

Enrollment period: 2 years (Sept. 2008–Aug. 2010)

Follow-up period: 5 years after last enrollment

Cumulative study period: 7 years (Sept. 2008–Aug. 2015)

# **1. Study Objectives**

The purpose of this study is to determine the optimal dosing period of capecitabine as postoperative adjuvant chemotherapy in cases of Stage III (Dukes’ C) colorectal cancer and sigmoid colon cancer involving curative resection by comparing patients receiving 8 courses (approximately 6 months) of the standard-of-care therapy consisting of capecitabine administered in a 2 weeks on, 1 week off schedule (Group A) with patients receiving 16 courses of capecitabine (approximately 12 months) on the same dosing schedule (Group B).

Primary Endpoint:

Disease-free survival (DFS) period

Secondary Endpoints:

(1) Relapse-free survival (RFS) period

(2) Overall survival (OS) period

(3) 2-year DFS rate

(4) Adverse event frequency and severity

(5) Treatment compliance

(6) HRQOL (Health-related Quality of Life)/Medical Economy　*Tertiary study conducted by capable study sites

# **2. Study Background**

## **2-1. Overview of Target Disease**

**2-1-1. Colon Cancer Epidemiology**

The number of colon cancer cases in Japan increases every year. This figure was estimated at 60,732 cases in 1990, and rose sharply to approximately 100,137 cases in 2001 (a prevalence of approximately 78.7 cases per 100,000 people). In addition, colon cancer has become the second most common type of cancer in men, after gastric cancer, and the most common type of cancer in women. In terms of mortality frequency, 24,778 people died from colon cancer in Japan in 1990, and this figure rose to 41,097 people by 2005 (a mortality rate of approximately 32.7 deaths per 100,000 people). Colon cancer has become the fourth most common form of cancer in men (preceded by lung, gastric, and liver cancers), and the most common form of cancer in women 1).

**2-1-2. Colorectal cancer prognosis**

The first-line treatment option for colorectal cancer is surgery, but according to a national survey conducted by the Japanese Society for Cancer of the Colon and Rectum (JSCCR), the 5-year survival rate by stage classification in colon cancer treated with radical surgery is 90.4% for Stage I, 82.0% for Stage II, 69.2% for Stage III, and 15.9% for Stage IV. Meanwhile, the 5-year survival rate by stage following surgery for rectal cancer is 91.4% for Stage I, 76.4% for Stage II, 57.5% for Stage III, and 14.6% for Stage IV 2). As such, although the respective 5-year survival rates for Stage I and Stage II cases are relatively favorable, the recurrence rate for Stage III cases is high, and adjuvant chemotherapy administered with the aim of suppressing postoperative cancerous recurrence is necessary in the treatment of colorectal cancer. The appropriate utilization of postoperative adjuvant chemotherapy is believed to ultimately contribute to improved survival prognosis in cases of colorectal cancer.

## **2-2. Postoperative adjuvant therapy for colon cancer**

**2-2-1. Postoperative adjuvant therapy for colon cancer**

In Europe and the United States, the results of the Intergroup, NSABP, and IMPACT studies conducted primarily by the North Central Cancer Treatment Group (NCCTG) in the 1990s demonstrated the clinical utility of postoperative adjuvant chemotherapy surgery alone in Stage III colorectal cancer cases. Additionally, 5-FU + LEV chemotherapy was designated as a standard treatment for Stage III colorectal cancer at the National Institutes of Health (NIH) consensus conference in 1990. 5-FU + LEV chemotherapy was subsequently established as the control arm for this comparative study. Results of subsequent clinical studies, such as the INT0089 study, suggested there was little benefit in adding LEV to 5-FU + LV therapy, that 5-FU + high-dose LV and 5-FU + low-dose LV demonstrated similar performance, and that 5-day continuous administration and once-weekly administration of LV also achieved similar performance 3)-7). Based on these results, 5-FU/LV therapy was established as the standard-of-care for postoperative adjuvant chemotherapy for Stage III colorectal cancer cases. In addition, studies investigating oral 5-FU were also conducted. In the NSABP C-06 study investigating UFT + LV therapy in Stage II/III colorectal cancer cases, UFT + LV exhibited noninferiority compared with 5-FU/LV (disease-free survival [DFS]: hazard ratio [HR] 1.004, overall survival [OS]: HR 1.014) 8). In the X-ACT study of capecitabine for Stage III colorectal cancer, not only was noninferiority of capecitabine monotherapy (DFS: HR 0.86, OS: HR 0.84) demonstrated in comparison with 5-FU/LV therapy, but significant trends were also observed during the superiority study, and significant improvement was observed with respect to relapse-free survival (RFS) 9). Combination therapies containing oxaliplatin and irinotecan hydrochloride were also evaluated, and significant improvement in DFS was not observed with the use of irinotecan hydrochloride in the CALGB C89803, ACCORD-02, or PETACC-3 studies 10)-12). Meanwhile, oxaliplatin demonstrated significant improvements in DFS in the MOSAIC and NSABP C-07 studies 13), 14).

Many Japanese studies of oral 5-FU drugs have also been conducted. Individual tests of a surgery only patient group have failed to demonstrate the superiority of oral 5-FU drugs, but the results of a meta-analysis of the No. 7 and No. 15 studies conducted by the Japanese Foundation for Multidisciplinary Treatment of Cancer (JFMC) revealed that 1 year of oral 5-FU drug therapy was significantly superior in terms of DFS and OS in Stage III colorectal cancer cases 15). Randomized controlled trials (RCTs) investigating 5-FU/LV therapy and UFT + LV therapy for Stage III colorectal cancer are currently underway in Japan.

**2-2-2. Standard postoperative adjuvant chemotherapy regimens for colorectal cancer recommended by Japanese and overseas guidelines**

The following treatment regimens are recommended in the Japanese “JSCCR Guidelines 2005 for the Treatment of Colorectal Cancer” and the American National Comprehensive Cancer Network (NCCN) Clinical Practice Guidelines in Oncology 2008 (NCCN Guidelines®) v.1.

Table 1 Standard postoperative adjuvant chemotherapy regimens for colorectal cancer recommended by Japanese and overseas treatment guidelines

| Guideline | Regimen | No. of courses/dosing period |
| --- | --- | --- |
| Guidelines for the treatment of colon cancer | 5-FU/LV therapy (RPMI regimen: bolus) | 6 months |
| NCCN  Guidelines* | 5-FU/LV(RPMI regimen: bolus) | 4 courses (8 months) |
| 5-FU/LV(Machover regimen: bolus) | 6 courses (6–7.5 months) |
| Capecitabine (2,500 mg/m2 twice daily on days 1–14 (repeat every 3 weeks) | 8 courses (6 months) |
| 5-FU/LV + oxaliplatin(FOLFOX4 regimen: infusion) | 12 courses (6 months) |
| 5-FU/LV + oxaliplatin(mFOLFOX6 regimen infusion) | 12 courses (6 months) |

* The National Comprehensive Cancer Network (NCCN) Clinical Practice Guidelines in Oncology (NCCN Guidelines®) concern Category 2A or higher

**2-2-3. Period of postoperative adjuvant chemotherapy for colon cancer**

Drug selection and administration period with respect to postoperative adjuvant chemotherapy for colorectal cancer were evaluated in the following 3 studies. In the INT-0089 study targeting high-risk Stage II and Stage III colorectal cancer cases, 5-FU/LEV (12 months) was administered to the control group, and 5-FU/LV (low-dose LV: 6 months) and 5-FU/LV (high-dose LV: 8 months), and 5-FU/LV+LEV (low-dose LV: 6 months) were administered to the experimental groups. Comparison with respect to DFS and OS revealed no significant differences between the groups, and it was determined that 5-FU/LV (6 months) is preferable to 5-FU/LEV (12 months) in terms of toxicity, cost, and patient burden 3). The NCCTG 894651 study also compared 4 groups of high-risk Stage II and Stage III colorectal cancer cases receiving 6-month or 12-month administration of 5-FU/LEV. Six-month administration of 5-FU/LEV/LV demonstrated a significantly better 5-year survival rate compared with 6-month 5-FU/LEV, but no significant difference was observed between 12-month 5-FU/LEV and 12-month 5-FU/LEV/LV. Moreover, in the NSABP C-04 study evaluating the efficacy of 5-FU/LV (once weekly), in comparison to 12-month 5-FU/LEV and 5-FU/LEV/LV as treatment for Stage II/III colorectal cancer, once weekly 5-FU/LV demonstrated significantly better DFS when compared with 12-month 5-FU/LEV, and no significant difference when compared to 12-month 5-FU/LEV/LV 16).

Based on the above observations, 6 months was determined to be the standard treatment period for postoperative adjuvant chemotherapy for colorectal cancer.

In addition, because capecitabine and UFT-LV in the X-ACT and NSABPC-06 studies, respectively, were administered over 6-month periods, 6 months has also become the standard administration period for oral 5-FU drugs administered as part of postoperative adjuvant chemotherapy regimens for colorectal cancer.

However, because the test results forming the basis for this designation did not have sufficient detection sensitivity during their respective treatment periods, and because there were differences in the treatment periods among these studies, the National Cancer Institute Physician Data Query (NCI PDQ) states that the current evidence supporting this treatment period is not definitive.

In addition, the results of a meta-analysis indicated that 1-year administration of oral 5-FU drugs in Stage III colorectal cancer cases achieved significantly superior DFS and OS compared to the surgery only group 15), and in numerous Japanese clinical trials, the period of administration for oral 5-FU drugs is often set as 1 year or longer, so it cannot be concluded that the optimal treatment period for oral 5-FU drugs as adjuvant postoperative chemotherapy for colorectal cancer is 6 months. Currently, the JFMC33-0502 (No. 33) study conducted by the JFMC is evaluating daily UFT/LV (6 months) in comparison to UFT/LV administered in 5 doses over 2 days (18 months).

**2-2-4. Relationship between treatment period and time to cancerous recurrence in postoperative adjuvant chemotherapy for colorectal cancer**

The hazard function was estimated using the colorectal cancer-related data from JFMC studies No. 7 and No. 15 as well as the X-ACT study data, and was used to assess the timing and risk of cancerous recurrence.

Changes in the risk of recurrence between the surgery only group and the 1-year oral 5-FU drug therapy (UFT, HCFU) group are shown in Fig. 1. Changes in the recurrence risk in the 6-month 5-FU/LV group and the 6-month capecitabine monotherapy group during the X-ACT study are shown in Fig. 2.

The recurrence risk in the surgery only group, 6-month 5-FU/LV, and 6-month capecitabine monotherapy groups peaked between 1 and 2 years postoperatively. However, no peak recurrence risk was observed in the 1-year oral 5-FU drug therapy (UFT, HCFU) group.

Fig. 1 JFMC No. 7 and No. 15 studies: differences in recurrence risk between Stage II/III colorectal cancer patient groups receiving surgery only or oral 5-FU drug therapy for 1 year

DFS

Surgery-only group　　　　　　　1 year of oral 5-FU drug group

Fig. 2 X-ACT study: differences in recurrence risk between Stage III colorectal cancer patient groups receiving 5-FU/LV therapy for 6 months or capecitabine monotherapy for 6 months

DFS

## **2-3. Profile of Capecitabine**

**2-3-1. Overseas clinical trials investigating postoperative capecitabine monotherapy for colon cancer**

In early 1998, oral capecitabine (1,250 mg/m2, twice daily for 21 days, administered continuously on days 1–14, off-drug for the final 7 days) was administered postoperatively to 1956 patients with Dukes’ Stage C colorectal cancer via rapid intravenous injection as part of a randomized Phase III comparative study against 5-FU/LV (Mayo Clinic regimen) (6 month treatment period for each group). In the safety analysis group (993 patients in the capecitabine treatment group, 974 patients in the rapid IV 5-FU/LV group), patients in the capecitabine group exhibited significantly lower incidences of diarrhea, stomatitis, nausea/vomiting, and neutropenia in comparison to the 5-FU/LV group (*p*<0.001), but higher incidence of hand-foot syndrome. The number of patients who developed Grade III or IV neutropenia, febrile neutropenia/sepsis, or stomatitis was lower in the capecitabine group compared with the 5-FU/LV group (*p*<0.001). However, the number of patients who developed Grade III hand-foot syndrome was higher in the capecitabine group (*p*<0.001). The safety profile of capecitabine was similar in patients under and over 65 years of age 17). Regarding DFS, the primary endpoint of this study, capecitabine was demonstrated to have achieved equal or superior results compared with rapid IV 5-FU/LV (Mayo Clinic regimen) (HR 0.87 [95% confidence interval (CI): 0.75-1.00]) 18).

**2-3-2. Overseas clinical trials investigating postoperative capecitabine monotherapy for metastatic colon cancer**

Two multicenter, open-label Phase III clinical studies were jointly conducted to compare intermittent administration of capecitabine against rapid intravenous 5-FU/LV (Mayo Clinic regimen, the standard regimen designated by regulations at the time) as first-line treatment for metastatic colorectal cancer 19, 20). The same protocol was used for these studies, and an integrated analysis of all data was prospectively designed. A total of 1207 patients received oral capecitabine (1,250 mg/m2, twice daily for 21 days, given continuously for days 1–14, off-drug for the final 7 days; n=603) or rapid intravenous 5-FU/LV (Mayo Clinic regimen; n=604). Patients who received capecitabine exhibited significantly better response rates compared with the 5-FU/LV group (26% vs. 17%; *p*<0.0002). The median time to response, time to effect loss, and duration of response were all similar across the groups. In addition, the times to disease progression (TTP) were comparable between the groups (capecitabine and 5-FU/LV, median period: 4.6 and 4.7 months, respectively). The survival periods were also comparable (median periods: 12.9 and 12.8 months, respectively). A subgroup analysis revealed that capecitabine administration consistently resulted in superior response rates (*p*<0.05) even in the patient subgroup with poor prognostic indicators. Multivariate Cox regression analysis confirmed that poor performance status (PS) (Karnofsky Performance Status [KPS] ≤ 80 vs 100), liver as the primary site of metastasis, and multiple metastases vs. single metastasis were independent prognostic indicators of low survival rate 21).

Based on these results, capecitabine was approved by various regulators worldwide as a first-line monotherapy for patients with metastatic colorectal cancer.

**2-3-3. Overseas Phase II clinical trials targeting nonresectable colon cancer**

In an overseas study investigating the safety and efficacy of capecitabine, 1,250 mg/m2 of capecitabine was orally administered twice daily for 21 days continuously with a 7-day off-period to 60 patients with nonresectable colorectal cancer who were chemotherapy-naïve or who had completed preoperative or postoperative adjuvant chemotherapy 6 months prior. A response rate of 35.0% was observed, and major adverse events included hand-foot syndrome in 73.3% of patients, skin discoloration in 38.3%, diarrhea in 35.0%, nausea in 35.0%, stomatitis in 35.0%, and diminished appetite in 33.3% of patients 22).

# **3. Selection Criteria**

## **3-1. Inclusion Criteria**

1) Patients histologically diagnosed with colon cancer (adenocarcinoma)

2) Cases of histological Stage III* colorectal cancer or sigmoid rectal cancer

*as defined in the Treatment Guidelines for Colorectal Cancer (7th edition)

3) Colorectal cancer cases in which resective surgery was performed (including cases involving D2 or higher lymph node dissection)

4) Cases in which surgery was determined to have achieved cure degree A (Cur A)

5) Patients aged (at time of enrollment) between 20 and 80 years

6) Performacne Status (PS) (Eastern Cooperative Oncology Group [ECOG]): 0 or 1

7) Eligible patients who have not yet undergone chemotherapy or radiotherapy

8) Patients capable of taking meals

9) Patients maintaining stable vital organ functions

a) WBC count ≥ 3,000/mm3 and <12,000/mm3

b) Hemoglobin ≥ 9.0 g/dL

c) Thrombocyte count ≥ 90,000/mm3

d) Serum creatinine ≤ 1.5x hospital standard upper limit

e) Total serum bilirubin ≤ 1.5x hospital standard upper limit

f) AST, ALT ≤ 2.5x hospital standard upper limit

g) ALP ≤ 2.5x hospital standard upper limit

10) Creatinine clearance* >50 mL/min

*: Determined based on the following simple formula to calculate creatinine clearance

Men: [(140-age)×body weight (kg)]/[72×serum creatinine value (mg/dL)]

Women: [(140-age)×body weight (kg)×0.85]/[72×serum creatinine value (mg/dL)]

11) Cases in which the protocol treatment was initiated within 8 weeks after surgery

12) Patients who consented to study participation in writing

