## **4-2. Subject Enrollment**

This study utilized centralized subject enrollment.

1) Register so that treatment can be started within 8 weeks after the date of surgery after confirmation of eligibility under “3. Selection Criteria”. (Note: enroll after confirmation of pathological test results)

2) After obtaining patient consent to study participation, fill out the "case registration form" (Form 1-1) and send to the secretariat via fax.

3) After receiving the case registration form via fax, the secretariat confirms that the prospective subject meets the selection criteria, then calls the study site supervisor as soon as possible. Subject group assignment then occurs, and dosing based on the subject total body surface area is communicated to the site by the secretariat, completing subject “enrollment”. The study secretariat then promptly sends the case registration confirmation form (Form 1-2) to the study site. Each site retains the case registration confirmation form on site and manages subject identification by creating a subject registry, etc.

4) The protocol treatment is initiated within 14 days after enrollment.

* “As soon as possible” means for subject enrollment (9:00-17:00) during business hours (Monday-Friday, excluding public holidays and the Year-End holiday period [December 29-January 4]), within “30 minutes” when submitted via paper during business hours (9:00-17:00) or between 9:00-9:30 the following business day if submitted outside of business hours (e.g., 9:00-9:30 on the next working day).

Japanese Foundation for Multidisciplinary Treatment of Cancer

[name]

[contact] (data center)

[name] (study representative/administration)

[name] (toll-free)

[contact]

E-mail: [contact] (data center)

Hours: Monday-Friday, 9:00-17:00 (excluding weekends, national holidays, and the New Year period (12/29–1/4))

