## **5-5. Treatment Discontinuation Provisions**

**5-5-1. Treatment discontinuation criteria**

If applicable, the attending physician will discontinue subsequent treatments and take appropriate measures. Investigators should observe and inspect for the evaluation items specified in “Table 6 Examination items and evaluation schedule” below at the time of discontinuation and record their findings and the accompanying rationale in their case report. In cases of termination, the attending physician shall promptly submit an administration progress survey to the study secretariat via fax.

1) When a subject him/herself withdraws consent

2) When a subject him/herself requests discontinuation of the protocol treatment

3) When recurrence of the original disease is observed

4) When novel cancerous lesions (duplicated cancer or multifocal colorectal cancer [excluding M cancer]) occurs

5) When the attending physician determines that protocol continuation will be difficult due to deterioration of comorbidities or onset of complications

6) When there is no relief or disappearance of symptoms following withdrawal due to an adverse event that falls under the off-period/dose reduction provisions (delay of treatment start by over 3 weeks or withdrawal)

7) If administration cannot be continued due to the occurrence of an adverse event even after 1 or 2 level reductions under the off-period/dose reduction provisions

8) If an adverse event of Grade IV occurs, the protocol treatment must be discontinued. (If capecitabine treatment is restarted at the discretion of the attending physician after protocol termination, a case report must be submitted.)

9) When the attending physician determines that protocol continuation will be difficult owing to an adverse event

10) If a subject dies

11) When the protocol treatment cannot be continued because the subject was transferred to a hospital

12) If a subject is determined to be ineligible after enrollment

13) Other cases in which the attending physician deems it necessary to terminate the protocol treatment

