# **8. Statistical Matters (Research Evaluation Criteria and Analyses)**

## **8-1. Definition of the Target Population for Analysis**

1) All enrolled subjects: The group of all enrolled subjects excluding duplicate or invalid enrollments.

2) All eligible subjects: The group of all enrolled subjects excluding “ineligible subjects”. However, ineligible subjects are defined as subjects determined to not meet the selection criteria after enrollment, or cases in which it becomes clear that the subject meets 1 or more of the exclusion criteria.

3) All treated subjects: The group of all enrolled, qualified subjects excluding those for whom the protocol treatment was not completed.

Based on the above definitions, the main subject groups targeted for the analysis of efficacy and safety shall be all enrolled subjects and all treated subjects.

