## **8-2. Primary Endpoint Analyses**

1) The main objective of this study is to evaluate the superiority of the study drug in terms of the disease-free survival (DFS) of group B (test treatment group: 16 courses administered) compared with group A (standard treatment group: 8 courses administered). The median annual DFS for all enrolled subjects is estimated by group using the Kaplan-Meier method. Greenwood’s formula is used for interval estimation. For the evaluation of the hypothesis, the stratified log-rank test, which considers a layer composed of a combination of allocation adjustment factors excluding study sites, is used. If the one-sided significance level is 5% and it is demonstrated that group B exhibits statistically significantly superior performance compared with group A, group B will be regarded as the standard therapy replacing the group A therapy. If group B’s performance is inferior to group A, the standard therapy will remain unchanged.

2) The stratified Cox proportional hazard model will be used. This model considers the layer composed of the combination of allocation adjustment factors other than study site as an estimate of the treatment effect. The hazard ratio of the treatment effect among the groups and its 95% confidence interval will also be obtained. A Wald-type estimator is used to estimate confidence intervals. If necessary, in addition to the allocation adjustment factor, an adjusted hazard ratio accounting for background bias will be derived.

3) A similar secondary analysis will be carried out for all eligible subjects.

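### Inclusion criterion 11 is worded as a treatment start that happens after randomisation, so under 8-1 a late or missing start makes a randomised patient ineligible and removes them from the secondary all-eligible DFS analysis

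*Protocol*

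**What the plan says.** Criterion 11 in Protocol 3-1, repeated word for word in the synopsis (0-3-1), admits "Cases in which the protocol treatment was initiated within 8 weeks after surgery".

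Protocol 4-2 sets the order of events. Sites are told "Register so that treatment can be started within 8 weeks after the date of surgery after confirmation of eligibility". The secretariat checks the selection criteria, "Subject group assignment then occurs", and then "The protocol treatment is initiated within 14 days after enrollment". Section 5-1 gives the same 8-week limit as a rule for treatment that has already been assigned.

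Protocol 8-1 counts as ineligible those "subjects determined to not meet the selection criteria after enrollment", together with anyone later found to meet an exclusion criterion. The all-eligible set is all enrolled subjects minus these. The all-treated set is limited to qualified subjects and also leaves out those who did not complete protocol treatment. Section 8-1 names all enrolled and all treated subjects as the main sets for efficacy and safety.

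Protocol 8-2 runs the primary DFS analysis in all enrolled subjects and adds: "A similar secondary analysis will be carried out for all eligible subjects".

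Protocol 5-5-1, item 12, lists as a reason to discontinue protocol treatment: "If a subject is determined to be ineligible after enrollment".

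**The concern.** An eligibility criterion should be decidable from what is known when the patient is randomised. Criterion 11 is not: it describes something that happens, or fails to happen, once the group has been assigned. Section 8-1 does not limit the eligibility judgement to information available at enrolment, so failing criterion 11 later counts as ineligibility.

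The all-eligible DFS analysis would then exclude patients because of their behaviour after allocation, and what remains would no longer be protected by randomisation. The site is told the assignment before treatment starts, the arms differ by 8 versus 16 courses, and no placebo is described. A decision to delay or decline treatment could therefore be influenced by the arm. On the safety side, a late starter who took the whole planned course would be missing from the set meant to describe toxicity.

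**Working it through.** The point rests on the order of events and the set definitions. The protocol states no figure that could be reproduced.

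**Step 1: when criterion 11 can be known.** The sequence in 4-2 is: eligibility check, group assignment, then treatment within 14 days of enrolment. Criterion 11 concerns the last step, so it is undecided at the first.

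**Step 2: whether the time limits alone guarantee it.** The 8-week limit is 8 × 7 = 56 days after surgery. A patient enrolled on postoperative day *d* may start, by the 14-day rule alone, as late as day *d* + 14.

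- *d* = 42: latest start is day 42 + 14 = 56, so the 8-week limit holds across the whole window.
- *d* = 43: latest start is day 43 + 14 = 57, so the 8-week limit can be missed.
- *d* = 56: latest start is day 56 + 14 = 70.

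A patient enrolled on days 43 to 56 could therefore have been properly registered under 4-2, start inside the 14-day window, and still fail criterion 11. Applying both limits together removes the inconsistency in the instructions to the site. It does not settle how 8-1 classifies a patient who in fact started late.

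**Step 3: tracing patients through the sets in 8-1, read literally.**

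| After allocation | All enrolled (primary DFS) | All eligible (secondary DFS) | All treated |
| --- | --- | --- | --- |
| Starts by day 56, completes | in | in | in |
| Starts by day 56, does not complete | in | in | out: completion clause |
| Starts after day 56, completes | in | out: criterion 11 | out: criterion 11 |
| Starts after day 56, does not complete | in | out: criterion 11 | out: either reason |
| Never starts | in | out: criterion 11 | out: either reason |

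Criterion 11 changes the all-eligible set for both late and never-starters. In the all-treated set it makes the difference only for late starters who complete. Item 12 of 5-5-1 bears on that same group, since a late starter classed as ineligible falls under a listed reason for discontinuation.

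**Step 4: size.** The protocol gives no rate of late or missing starts. With an assumed range of 1% to 5%:

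- 0.01 × 1,200 = 12 patients
- 0.05 × 1,200 = 60 patients

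This range covers late and never-starters together, so it applies to the all-eligible set. The number lost from the all-treated set because of criterion 11 alone is smaller and cannot be estimated from the document.

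**The case against.** The strongest reply is that the past tense comes from translation. The protocol uses it for other planned acts, for example enrolment in 4-2 and the interim analyses in 8-7. Read literally, criterion 11 would prevent all enrolment, because nobody has started treatment when the secretariat checks eligibility. Section 4-2 shows the workable, prospective meaning. This is plausible, and it probably is what was intended. It does not remove the problem: the wording stands in both lists of criteria, and 8-1 acts on the criteria without limiting the judgement to what was known at enrolment.

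Four stronger readings might be inferred, and the protocol does not support them:

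- **That the main result is at risk.** The primary DFS analysis uses all enrolled subjects, whom criterion 11 cannot remove.
- **That criterion 11 is what removes never-starters from the treated set.** The completion clause in 8-1 removes them, and all non-completers, in any case. Rewording criterion 11 would not change that.
- **That late starts will differ by arm.** Section 8-4 describes treatment in the first 6 months as essentially the same in both groups, and a patient unwilling to take 12 months could start on time and stop later. Slow postoperative recovery would have nothing to do with the arm. Dependence on arm is possible because the allocation is known, but nothing in the protocol shows it.
- **That 4-2 contradicts criterion 11.** Both give 8 weeks, and 4-2 does not say what follows from a late start. They differ in wording and function, not in the limit.

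It is also fair that an all-eligible analysis is never a full randomised comparison. But excluding a patient for a baseline fact discovered late is different from excluding one for what happened after allocation.

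**Conclusion.** The point holds as a minor defect of wording with a definite consequence. Followed as written, criterion 11 and 8-1 together exclude randomised patients from the secondary all-eligible DFS analysis because of a post-allocation event. They also exclude late starters who completed treatment from the all-treated set. The primary analysis is untouched.

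The size is unknown: 12 to 60 of 1,200 patients for the all-eligible set under an assumed 1% to 5%, with no rate in the protocol to support either end. The conclusion assumes that 8-1 is applied literally. It also assumes that the all-treated set is the one used for safety; 8-1 names the two main sets for efficacy and safety without spelling out the pairing. If the sponsor already reads criterion 11 prospectively, the text should say so.

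**What to change.** 1. In 0-3-1 and 3-1, word criterion 11 as a condition that can be judged at enrolment, in line with 4-2 ("Register so that treatment can be started within 8 weeks after the date of surgery").
2. In 8-1, state that eligibility for the analysis sets is judged only on the patient's status before randomisation, and that a late or missing start is recorded as a protocol deviation for analysis and does not make the patient ineligible.
3. Reconcile 0-3-1, 3-1, 4-2, 5-1, 5-5-1 (item 12) and 8-1, so that it is clear where the 8-week limit is an entry condition and where it is a rule of conduct, and how it sits with the 14-day window. The clinical handling of a patient who starts late is for the sponsor to decide.

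The cost is a few sentences. No patients, visits or analyses are added, and the sample size is unchanged.
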